
### Patient Retention and Follow-Up

As noted above, we plan to pilot tracking of patients through different phases and venues of care to ensure that we retain all enrolled patients. Most of the patient data will be collected during the prehospital, ED, and hospital phases of care, so patient retention beyond the initial hospitalization is not expected to an issue for our primary endpoint. Collection of the follow-up modified Rankin Scale at 3 months (a secondary endpoint) will be facilitated by engagement of patients by local stroke coordinators at the time of their hospitalization.

### Mixed Methods Sample Estimates

Planned mixed methods data collection by stakeholder group including planned number of focus groups, surveys, and interviews is shown in Table 4. We will sample from each EMS region and adjust sampling strategy to account for the small number of stroke centers in EMS regions 2 and 4 to reach saturation (46) within and across groups. We plan to foster engagement of stakeholder groups in various ways to achieve adequate participation. Involvement of EMS will be facilitated by EMS regional directors and advisory councils, and stroke center coordinator and director participation will be promoted by regional educational conferences described above.

**Table 4 T4:** Mixed methods data collection by stakeholder group.

**Stakeholder group**	**Stroke system role**	* **N** *	**Pre-implementation**	**Post-implementation**
**Alabama Trauma Communications Center**	Prehospital stroke care coordination	19	2 Focus groups (*n* = 19)	Survey (*n* = 19)
				Interviews (*n* = 12)
**EMS Regional Directors and Advisory Councils**	OEMS and EMS coordination	72	Individual interviews with Regional Directors (*n* = 6)	Regional Advisory Council Survey (*n* = 72)
				Interviews (*n* = 36)
**EMS**	Stroke assessment, care, triage	4,800	6 Focus groups (*n* = 48–72)	Survey (*n* = 600)
				Interviews (*n* = 36)
**Stroke Center Coordinators**	Stroke center care coordination	69	5 Focus groups (*n* = 40–60)	Survey (*n* = 69)
				Interviews (*n* = 30)
**Stroke Center Directors**	Stroke center leadership	69	Individual interviews (*n* = 30)	Survey (*n* = 69)
				Interviews (*n* = 30)

*EMS, Emergency Medical Service: OEMS, Office of Emergency Medical Services*.

### Statistical Analysis of Stepped Wedge Data

TCC Coordinated SBST will be implemented sequentially, thus leading to a stepped wedge design. For the primary endpoint, to account for the dependency among repeated observations over time, generalized linear mixed models and generalized estimating equations will be employed to model a binary outcome with a logit link function. However, we will explore other distribution possibilities (i.e., probit; log-binomial; negative binomial) to develop the best fitting model. For secondary endpoints that are categorical or ordinal (i.e., proportion treated with tPA; Rankin scores), we will use similar approaches. For secondary endpoints that are more continuous (e.g., time to tPA treatment), we will use linear mixed models assuming a normal distribution and Cox regression for survival analysis. Missing data will be analyzed by creating an indicator code for missingness to assess whether the missingness is systematic. If we conclude the data are missing at random then we will use multiple imputation and compare results with and without the imputation methodology. If we determine that the missingness is systematic, we will conduct sensitivity analyses to examine the extent the missing data have on the results, interpretations, and conclusions of the study.

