### Design of the Stepped Wedge Cluster Trial

This is a hybrid type 1 effectiveness-implementation study with a multi-phase mixed methods sequential design and an embedded observational stepped wedge cluster trial. For an overview of how the study elements fit together see the study flowchart (Figure 2). The change in health care policy by the ADPH allows a natural experiment. Given available resources and the complexity of the intervention, the ADPH has planned a phased rollout, lending itself to analysis as a stepped wedge cluster trial with each EMS region serving as a cluster (21, 22). A stepped wedge cluster trial is appropriate given the existing evidence in support of stroke system change, the logistical need for sequential rollout, and the plan for the entire state (i.e., all clusters) to eventually implement the system change. This design will facilitate modeling the impact of time on the effectiveness of TCC Coordinated SBST. This study will broadly and equitably target a population of stroke patients of all ages, sexes, races, and ethnicities. A strength of this study is that at least 50% of subjects will be women and over one-third of the enrolled patients will be African Americans based on census data. As the study involves rural and urban regions and stroke centers of all levels across the State, we will gain information regarding the impact on resources (e.g., EMS response times for non-stroke conditions), benefits, and potential risks (e.g., delay to tPA treatment and other unintended consequences) of implementation across a wide range of service delivery contexts. Finally, because the trial is embedded within expanded LifeTrac data collection on all stroke system patients as well as system level data captured by ADPH, we will be able to evaluate its public health impact.

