### Randomization

Not applicable as this is a stepped wedge trial with the order of regional implementation determined by the ADPH.

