### Interim Analysis of Stepped Wedge Data

The stepped wedge nature of the data allows opportunity for Interim Analyses after TCC Coordinated SBST is implemented in EMS Regions 3 and 5. Interim analysis of the primary endpoint will be used to guide power analysis for future data collection. Interim analysis on secondary endpoints will be used to optimize training and delivery of TCC Coordinated SBST for Regions 1, 2, 4, and 6.

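### The roll-out order is not random, but the primary model is not stated to include EMS region as a fixed effect, so stable regional differences can leak into the SBST effect

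*Protocol article*

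**What the plan says.** All places are in the Protocol article.

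- **Design of the Stepped Wedge Cluster Trial:** the phased roll-out lends itself to "analysis as a stepped wedge cluster trial with each EMS region serving as a cluster". There are six regions. The section mentions modelling of time, but no region term.
- **Randomization:** "Not applicable as this is a stepped wedge trial with the order of regional implementation determined by the ADPH".
- **Interim Analysis of Stepped Wedge Data:** the plan foresees "Interim Analyses after TCC Coordinated SBST is implemented in EMS Regions 3 and 5", and uses the secondary endpoints to "optimize training and delivery of TCC Coordinated SBST for Regions 1, 2, 4, and 6". Regions 3 and 5 are therefore first.
- **Statistical Analysis of Stepped Wedge Data:** "to account for the dependency among repeated observations over time, generalized linear mixed models and generalized estimating equations will be employed", with a binary outcome and logit link. The text adds that "we will explore other distribution possibilities" in search of the best fit. It lists no model terms: neither region, nor period, nor the SBST indicator.
- **Alabama Stroke System** and **Study Organization:** seven in-state thrombectomy centers are listed. Regions 3, 5 and 6 have two each, region 1 has one, and none is listed in regions 2 and 4.

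**The concern.** In a stepped wedge design, early regions tend to contribute relatively more after-implementation patients and late regions relatively more before-implementation patients. A mixed model or GEE draws on both the change within regions and the comparison between regions. The between-region part is unbiased only if a region's underlying thrombectomy rate is unrelated to when it crosses over. Random ordering would secure that on average, but here the order is an administrative choice and regions differ on the capability that the primary outcome measures.

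If the early regions already had better access to thrombectomy, SBST could appear to work when it did nothing. If they had worse access, a true benefit could be hidden. This needs no secular trend and no spillover between regions. Choosing the link or distribution by fit does not protect against it.

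**Working it through.** **1. The plan's own figures (Sample Size Estimates).** With n = (1.960 + 0.842)² × [p1q1 + p2q2 − 2r√(p1q1·p2q2)] / (p2 − p1)², two-sided α = 0.05 and 80% power:

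- 50% to 60%, r = 0.1: 7.849 × 0.4410 / 0.0100 = 346 per period.
- 50% to 57.5%, r = 0.5: 7.849 × 0.2472 / 0.005625 = 345 per period.

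Both agree with the stated figure of about 350. The improvements are therefore relative, and the planned 15% effect is an odds ratio (OR) of (0.575/0.425) / (0.50/0.50) = 1.35. The planned 1,200 to 1,300 observations match 423 × 3 = 1,269 patients with LVO. The calculation has no region effect.

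**2. Assumptions.** The article gives no regional thrombectomy rates, regional volumes or crossover dates in its text, and the timeline figure is not available. The following are assumed, with no SBST effect and no trend:

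- *Schedule A:* regions 3 and 5 cross at month 12 and the rest at month 24. Volumes are proportional to the stroke-center counts 14, 7, 17, 3, 17 and 11, so regions 3 and 5 carry 34 of 69.
- *Staggered schedule:* the same volumes, with crossovers from month 6 to about month 30.
- *Schedule C:* six equal regions over 12 quarters, with regions 3 and 5 crossing in quarters 3 and 4 and the rest in quarters 6 to 9.
- *Baseline gap:* regions 3 and 5 higher by 5, 10 or 20 points.

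Under schedule A, regions 3 and 5 supply 34×12 / (34×12 + 35×24) = 33% of before patients and 34×24 / (34×24 + 35×12) = 66% of after patients.

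**3. Independence GEE plus period, schedule A, in closed form.** In the first year no region has SBST and in the third year all have it, so the period terms absorb both. Only the middle year informs the SBST term, and there it compares regions 3 and 5 with the rest:

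- 5 points (52.5% v 47.5%): (0.525/0.475)² = 1.22
- 10 points (55% v 45%): (0.55/0.45)² = 1.49
- 20 points (60% v 40%): (0.60/0.40)² = 2.25

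A larger sample does not reduce this.

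**4. Spurious odds ratios, all models with calendar period.** N is 1,250 to 1,269 unless stated.

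| Model | 5 points | 10 points | 20 points |
|---|---|---|---|
| Independence GEE, schedule A (closed form) | 1.22 | 1.49 | 2.25 |
| Independence GEE, schedule C | 1.16 | 1.35 | 1.83 |
| Random intercept, schedule C (fit to expected data) | 1.16 | 1.31 | 1.13 |
| Random intercept, simulated, volumes by center count | not run | 1.20–1.25 | about 1.11 |
| Exchangeable GEE, schedule C (mean of 30 simulated data sets) | 1.17 | 1.19 | 1.11 |
| Random intercept, schedule C, N = 7,038 | 1.10 | 1.04 | 1.02 |
| Fixed region, schedule C | 1.00 | 1.00 | 1.00 |

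In simulation on schedule A and the staggered schedule, fixed region plus period gave 0.99 to 1.02.

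The random-intercept leak is not monotone in the gap. A small gap lets the estimated region variance fall towards zero, so the model behaves like the independence analysis. A large gap forces the variance up, and the model then relies on within-region change.

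**5. The N = 7,038 row.** This is 2,346 × 3, all suspected-LVO patients over 36 months, with the same assumed rates as the other schedule C rows. The plan's figures imply a lower thrombectomy rate in that group: 211 / 2,346 = 9.0%. Information on the logit scale goes as N·p·q, which gives 1,269 × 0.25 = 317, 7,038 × 0.09 × 0.91 = 576 and 7,038 × 0.25 = 1,760. For the same gap in log odds, that row is therefore a favourable case for the random-region model.

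**6. Rejection rates and precision.** At a 10-point gap, random region plus period rejected the true null in 14% to 23% of runs, across two sets of simulations (200 and 400 runs per setting). Fixed region plus period rejected in 7% to 8%. At 20 points the two sets disagreed for the random-region model (6.5–7.5% and 12–13%), so no weight is put on that figure. The SD of the log odds ratio, fixed against random region, was 0.26 v 0.27 on schedule A, and 0.20 v 0.20 or 0.23 v 0.22 on two staggered schedules.

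**The case against.** A reader might infer that the plan leaves region out of the model, or admits it only as a source of dependency. The article does not say this. Its analysis section lists no model terms, GLMM and GEE both accept region as a fixed factor, and an article may leave a covariate list to the full protocol or analysis plan. That objection stands against the stronger reading. What remains is that the section chooses the estimators and gives one reason for them, dependency, while another section sets randomization aside without naming any compensating adjustment.

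The size rests on assumptions, and this also stands. Capability does not divide cleanly by order: late region 6 has two thrombectomy centers, as regions 3 and 5 each do, and late region 1 has one. The documents do not show that regions 3 and 5 have higher thrombectomy rates, nor that they will supply most after patients.

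The leak is partial for a random intercept or exchangeable GEE, and it shrinks with larger regional samples. This matters because Primary Outcome counts suspected LVO, whereas the planned 1,200 to 1,300 matches the LVO count. At that planned size, however, the leak is material at modest gaps. The independence GEE, which the text does not rule out, does not improve with sample size.

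The fixed-region model also exceeded 5% rejection in simulation. Rejection rates alone therefore do not separate the two approaches; the bias in the odds ratio does.

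**Conclusion.** The concern holds as a conditional one. The order is non-random, the regions differ in thrombectomy capability, and the stated rationale for the primary model addresses dependency but not confounding by region. If region enters only as a random intercept or working correlation, time-constant regional differences can leak into the SBST effect.

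With about 1,250 observations, no true effect, no trend and a baseline 5 to 20 points higher in regions 3 and 5, the spurious odds ratio is about 1.1 to 1.3 with random region plus period. It is about 1.2 to 2.25 with an independence GEE plus period, and about 1.0 with fixed region plus period. The effect the trial is planned to detect is 1.35. With roughly 7,000 patients at the same assumed rates, the random-region figure falls to about 1.0 to 1.1. Gap, volumes and schedules are all assumptions.

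A reader might go further and conclude that the primary test will be biased or that its error rate is known to be wrong. The documents do not support that, because they give neither the model terms nor the regional rates. No corrected sample size follows from this point.

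**What to change.** In Statistical Analysis of Stepped Wedge Data, state that the primary model includes EMS region as a fixed six-level factor together with calendar period, so that SBST is estimated from change within regions. Report the random-region model as a sensitivity analysis.

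The cost is one sentence and five degrees of freedom, with essentially no loss of precision in the simulations. Inference becomes conditional on Alabama's six regions, which are all the regions in the state. The change removes only time-constant differences: it does not protect against regional trends that differ over time, and it does not settle how standard errors should be obtained with six clusters. Adjustment for patient characteristics is a separate question and is not needed for this point.

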## Methods and Analysis

### Alabama Stroke System

The statewide stroke emergency care system is managed by the ADPH Office of Emergency Medical Services (OEMS). Alabama counties are assigned to one of six EMS Regions shown in Figure 1. The OEMS oversees EMS Regional Agencies that provide initial contact for EMS concerns, provide effective communication between communities and the OEMS, assist EMS with rules compliance, provide local credentialing, and function as a clearing house for EMS education. In each region, established EMS Regional Directors and Advisory Councils are responsible for direct oversight and management of its specific regional stroke system. In 2017, the ADPH OEMS developed a statewide stroke system with three levels of stroke centers. Currently, the Alabama stroke system has 80 stroke centers, with 14, 7, 17, 3, 17, and 11 centers in EMS regions 1–6, respectively, and 11 out of state centers as shown in Figure 1. Level III centers (green dots) are acute stroke-ready hospitals, level II centers (blue dots) are primary stroke centers. There are three level I comprehensive stroke centers (yellow dots) in Alabama, the University of Alabama at Birmingham (UAB) in region 3; Southeast Health Medical Center, Dothan, in region 5; and University of South Alabama, Mobile, in region 6. Out of state comprehensive stroke centers include Erlanger Hospital, Chattanooga TN and Grady Memorial Hospital, Atlanta GA.

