### Sample Size Estimates for Stepped Wedge Cluster Trial

Based on 2018 data, the Alabama stroke system volume is about 7,630 over a 1-year period. Based on our pilot data (15), we estimate exclusion of 10% (763 patients) who are unresponsive or poorly responsive, and 5% (382 patients) with time last known well >24 h. We will allow for 10% missing EMSA data (763 patients), leaving 5,722 patients. Pilot data also indicate that over 1 year ~41% of this population (2,346 patients) will have EMSA ≥ 4 and be eligible for enrollment, 18% of enrolled patients (423 patients) will have LVO and be available for analysis of our primary endpoint, and ~50% of the patients with LVO are treated with MT (211 patients). Thus, for our power analyses, we will use 50% as the reference to examine whether implementation of TCC Coordinated SBST will be associated with a significant increase in the proportion of stroke system patients with suspected LVO who are treated with MT. Because of the Before-After nature of the data, a test that accounts for this dependency is necessary. However, even though these are repeated observations the dependency could be rather weak. Many of the same entities (e.g., hospitals, doctors, and paramedics) will be involve both before and after, the patients are very likely to be different; thus, leading to weaker dependency. To account for this possibility, we varied the strength of the dependency (correlation) from *r* = 0 to 0.5. Because the effect of implementing TCC Coordinated SBST is unknown, we varied the effect from small 10% to large 40% improvement. For a weak dependency of (*r* = 0.1), we would need ~350 subjects before and after to detect a moderate 20% improvement with 80% power at a α = 0.05 significance level. This corresponds to an increase of 35 patients treated with MT after TCC Coordinated SBST implementation. A smaller 15% improvement (increase of 26 patients treated with MT) with stronger dependency (*r* = 0.5) would also require ~350 subjects before and after to obtain 80% power at a α = 0.05 significance level. In either case, this data could be collected in ~20 months. Our sample size estimates are based on statewide stroke system entry volume data. Estimates of study eligibility volume and LVO frequency are based on methodology used in our preliminary study. However, to account for the possibility of smaller stroke system volume, smaller effect size, and/or weaker dependency, we plan on 36 months of data collection. For the proposed 36-month data collection timeline, with potentially 1,200–1,300 total observations, we should have more than adequate statistical power to detect a 15% improvement in the primary endpoint even with a weak dependency (*r* = 0.1) among observations.

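### The primary test is not fixed: two model families, six clusters and a distribution chosen by fit; if GEE is run with its ordinary inference, the 5% error rate is not held

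*Protocol article*

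**What the plan says.** The section Statistical Analysis of Stepped Wedge Data states that, for the primary endpoint, "generalized linear mixed models and generalized estimating equations will be employed to model a binary outcome with a logit link function". It continues that "we will explore other distribution possibilities (i.e., probit; log-binomial; negative binomial) to develop the best fitting model". Neither family is designated as primary, and no effect measure is named.

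Under Alabama Stroke System, "Alabama counties are assigned to one of six EMS Regions", and Design of the Stepped Wedge Cluster Trial describes the rollout as "lending itself to analysis as a stepped wedge cluster trial with each EMS region serving as a cluster". So there are six independent units. Under Randomization, "the order of regional implementation determined by the ADPH". Interim Analysis of Stepped Wedge Data shows that Regions 3 and 5 cross over before 1, 2, 4 and 6.

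The sample size section works at a 5% significance level and 80% power, for example "to detect a moderate 20% improvement with 80% power at a α = 0.05 significance level".

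**The concern.** Three faults lie in the text itself.

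- **Two families for one test.** GEE gives a population-averaged effect and GLMM a region-conditional one. With six clusters they also differ sharply in how far their usual tests can be trusted. If neither is primary, the same data can give two significance verdicts.
- **A model chosen by fit.** Logit gives an odds ratio, log-binomial a risk ratio, negative binomial a rate ratio, and probit a coefficient with no direct clinical reading. What will be reported is unknown until the outcome data have been modelled.
- **A count distribution for a binary outcome.** The negative binomial variance is at least the mean p, while a yes/no outcome has variance p(1-p).

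The small number of clusters makes the first fault costly. The sandwich variance of GEE and its z test rely on many independent clusters. The rollout order was not randomised, so no randomisation-based test can stand in and the inference rests on the model. What is at stake is the trial's main claim, that the new triage raises the proportion treated with thrombectomy.

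**Working it through.** **1. The plan's own sample size.** The article states no achieved type I error, so its sample size is the figure to reproduce. Inputs from the sample size section: reference 50%, alpha 0.05 (taken as two-sided; the article does not say), power 80%. The paired-proportions (McNemar) formula is n = [z_a·√pd + z_b·√(pd - d²)]² / d². Here d = p2 - p1, pd = p1 + p2 - 2·p11, and p11 = p1·p2 + r·√(p1·q1·p2·q2).

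- 50% to 60%, r = 0.1: p11 = 0.300 + 0.0245 = 0.3245, so pd = 0.451. n = (1.96·0.6716 + 0.8416·0.6641)² / 0.01 = 352.
- 50% to 57.5%, r = 0.5: p11 = 0.2875 + 0.1236 = 0.4111, so pd = 0.2528. n = (1.96·0.5028 + 0.8416·0.4972)² / 0.005625 = 350.

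Both match the stated figure of about 350 before and after. The formula contains the before-after correlation but nothing for six clusters, so it does not bear on the validity of the GEE or GLMM test.

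**2. Effect measure.** For the 15% relative improvement (50% to 57.5%), the risk ratio is 0.575/0.50 = 1.15 and the odds ratio is (0.575/0.425)/(0.50/0.50) = 1.35. Which one is reported depends on the model that fits best.

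**3. Type I error with six clusters.** The main null simulation used inputs from the article (six regions, 1,250 patients as the middle of 1,200-1,300, a 50% rate). The rest is assumed because the timeline figure is not shown: ICC 0, 0.01 or 0.05, some runs with region-by-period variation; one region per step, 2-2-2 or 1-1-2-2; time categorical, linear or absent; region sizes equal or in the ratio of stroke centres, 14:7:17:3:17:11. There were 300 replicates per scenario and 2,000 for six key ones. At a true 20%, the Monte Carlo SE is √(0.2·0.8/2,000) = 0.9 points, or 2.3 points with 300.

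| Test at nominal 5% | Rejection under no effect |
|---|---|
| GEE, uncorrected sandwich, z | 20.0-24.4% in key scenarios (20.0-21.5% with equal regions); 13-34% over the grid |
| GEE, Mancl-DeRouen, z | 6.6-9.9% |
| GEE, Mancl-DeRouen, t with 4 df | 2.0-3.9% |
| Random-intercept GLMM, likelihood ratio | 6.6-9.0% in key scenarios; about 3-14% over the grid |

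In one further setting, with about 7,000 patients and region-by-period variation, the GLMM reached 28%.

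A second simulation (seven periods, 3 × 423 = 1,269 patients, ICC 0.02, period effects fitted) gave:

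- 19% for exchangeable GEE with robust z (400 runs), and 18-22% for independence GEE over ICC 0.001-0.05;
- 5% for a logit with region and period terms, rising to 6-16% if regions drift differently;
- 4.7-5.7% for a region-by-period regression with a t reference. Its degrees of freedom are 6 × 7 = 42 cells less 6 + 6 + 1 = 13 parameters, or 29;
- 2.5-2.8% for Mancl-DeRouen with t on 4 df.

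A third run with seven periods and about 1,260 patients gave 18-23% for uncorrected GEE and 5-8% for the region-and-period logit.

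**4. Does choosing by fit add to this?** On independent null data, choosing by AIC among logit, probit, log-binomial and the Poisson limit of the negative binomial rejected 5.9%, against 5.6% for logit alone. With 1,000 runs the Monte Carlo SE near 5% is √(0.05·0.95/1,000) = 0.7 points, so the two do not differ detectably. The Poisson limit rejected 0.7% and was never selected.

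**5. Negative binomial.** Its model-based SE on the log scale is too large by a factor of at least 1/√(1-p). At p = 0.5 this is 1.41 (41%). At p = 0.18 × 0.50 = 0.09, the rate among all suspected-LVO patients, it is 1.05 (5%). The error is towards fewer false positives.

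**The case against.** The article names GEE but no variance estimator, working correlation, test statistic or degrees of freedom. Those details are commonly left to an analysis plan, which is not shown, and a correction may be specified there. This stands: silence about a small-sample correction is not a fault of the article, and the 20% figure is conditional on ordinary, uncorrected inference.

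A reader might infer that the plan as written runs at about 19-20% type I error. The documents do not support that. The figure applies to one of the two named families, in its uncorrected form, under an assumed ICC and rollout. GLMM, which is named first, is far less affected.

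A reader might also infer that the best-fit rule or the negative binomial drives false positives. The calculations show otherwise. Moreover, the 41% and 5% figures concern model-based standard errors and do not carry over to a sandwich variance.

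Finally, logit is the stated starting point, the alternatives are only to be explored, and nothing ties the choice to the treatment p-value. That is fair, and it softens the charge of choosing by result. It does not fix the model, because the stated aim of the exploration is the best-fitting one. An analysis plan that named a single model would have to override this wording rather than fill a gap in it.

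**Conclusion.** The concern holds as a fault in what the section fixes. One primary test is assigned to two families with no primary named, and its link and effect measure are left to fit. One candidate distribution is also wrong for a yes/no outcome.

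The consequence for error control is conditional. With six clusters, uncorrected GEE would reject a true null about 20% of the time in central scenarios (13-34% over the grid), roughly four times the stated 5%. A random-intercept GLMM would do so about 7-9% of the time (about 3-14% over the grid at 1,250 patients). These figures rest on the assumed ICC, rollout, time model and region sizes, and should be quoted as ranges. The inflation comes from the number of clusters. The best-fit rule and the negative binomial are separate faults of pre-specification and distribution.

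**What to change.** Before outcome data are examined, rewrite the primary analysis to name one model with a fixed link, a term for the new triage, and region and calendar-period effects, together with small-sample inference. Two workable choices are:

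- a region-by-period regression with a t reference (simulated error 4.7-5.7%);
- GEE with the Mancl-DeRouen correction and t on 4 df (2.0-3.9% in the main simulation, 2.5-2.8% in the second; conservative).

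State the effect measure that goes with the chosen model. Keep the other family, probit and log-binomial as sensitivity analyses. Delete the negative binomial and the best-fit rule.

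The change is to analysis wording only, and the Study Timeline section says enrolment had not begun at publication. The cost is wider confidence intervals and lower nominal power than the paired before-after calculation suggests.
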